## Summary

**Study title:** Brain Bootcamp: an initiative targeting dementia awareness and risk among older adults

**Protocol version** 1

**Overview** This project will be made up of 3 studies that aim to evaluate the impact of the public health campaign in improving dementia risk and dementia awareness, understand the facilitating factors to making and sustaining lifestyle changes, and to assess the acceptability and validity of a new cognitive assessment for older adults. These are described in detail below.

**Objectives**

Study 1 (i) To evaluate the impact of the Brain Bootcamp campaign in increasing dementia awareness and knowledge of modifiable lifestyle factors in older Australians

(ii) To evaluate the impact of the brain bootcamp campaign in improving older adults’ brain health risk profile

Study 2 To understand participants’ views of dementia prevention and the adoption of brain bootcamp into their daily lives

Study 3 (i) To determine the acceptability and feasibility of new virtual reality technology in assessing cognitive function in older adults

(ii) To assess the ability of the virtual reality technology to discriminate between cognitively intact and cognitively impaired participants

**Project design** **Mixed methods**

Study 1 Prospective pre post study

Study 2 Qualitative study

Study 3 Cross-sectional feasibility study

**Planned Sample Size**

Study 1 500 community-dwelling older adults residing in NSW

Study 2 40 older adults from Study 1 participants

Study 3 100 older adults (aged 65+) and 100 young adults (aged 18+)

**Selection criteria**

Study 1 and Study 2 Inclusion criteria

Population-based sample of community-dwelling adults aged over 65 years old

Exclusion criteria

Individuals with an active episode of major depression, an existing diagnosis of dementia, inability to provide informed consent, or are currently enrolled in any lifestyle change intervention

Study 3 Inclusion criteria

Population-based sample of community-dwelling adults aged over 18 years old

Exclusion criteria

Individuals with an active episode of major depression, an existing diagnosis of dementia, inability to provide informed consent, impairment of kinetic abilities (ability to use mouse), poor vision, unable to follow verbal commands, diagnosis of aphasia

**Study procedure**

Studies 1, 2, 3 Participants will be recruited via a widespread advertising strategy using flyer dissemination, banners and existing networks.

Study 1 Online MQ Qualtrics surveys will be given to eligible participants to capture demographics, participant’s dementia awareness, mental health and mood, physical activity, cognitive activity, diet, motivation, social networks and quality of life information data (i.e., baseline).

Upon completion of surveys, participants will receive a Brain Bootcamp Box via post containing four physical items representing modifiable risk factors for dementia, an information booklet and their personalised brain health risk profile.

Three months after the Brain Bootcamp box has been sent out, participants will fill out the same assessments (i.e. follow-up)

Study 2 A sample of participants from Study 1 will be invited to participate in a semi-structured interview at follow-up to explore their views of the Brain Bootcamp Box, whether they did/did not implement behaviour change (goal-setting, frequency of item use) and their opinion on the impact of the initiative.

Study 3 Participants from the general public will be recruited as well as a sample of participants from Study 1 will be invited to participate in a traditional and novel memory assessment based on their baseline assessments and dementia risk profile. These participants will engage in a virtual reality cognitive screener developed by Macquarie University, a telephone assessment of their cognition and a feedback questionnaire for their experience with the virtual reality cognitive screener.

**Statistical considerations**

**Sample size calculation**

Study 1 500 older adults are required to detect a meaningful change in dementia risk scores at two time points

Study 2 40 older adults will be suitable to sufficiently address the research question at hand and reach data saturation

Study 3 100 older adults and 100 adults will be recruited to determine sample size for this feasibility study

**Analysis plan**

Study 1 Descriptive analysis of baseline profile of participant demographics (age, gender, economic status) will be presented.

Non-parametric correlations and paired sample t-tests will be conducted to examine and analyse changes in primary outcome (dementia awareness, brain health risk profile) at baseline to three months.

**Study 2** Interview data will be analysed qualitatively for content and themes that emerge, and coded and categorised using N Vivo software

**Study 3** Descriptive statistics will be calculated for participant demographics and domains of the virtual reality screener and the traditional cognitive assessments. This will include percentage of participants who successfully completed the virtual reality cognitive assessments, time taken to complete the virtual reality cognitive assessment module, and scores from the feedback questionnaire.

Correlational analyses and receiver operating curve (ROC) will be conducted for performance scores on the virtual reality assessment module and scores on other cognitive assessment tests.

Duration of the Study 24 months

# 1. BACKGROUND AND INTRODUCTION

### 1.1. Literature Review

Dementia is one of the most common causes of disability, dependency and mortality among older adults and has considerable physical, psychological, social, and economic impacts on individuals diagnosed with dementia, their relatives, formal and informal caregivers, and society at large [1]. Cognitive ageing and dementia are global health priorities, with current estimates suggesting that 50 million people are living with dementia, with that estimate expected to triple by 2050 [2].

Despite extensive global research, there is no curative treatment for dementia [3]. However, there is considerable support for modifiable lifestyle risk factors as contributors to dementia development in later life [4]. Recent estimations suggest that one in three dementia cases may be attributable to common modifiable risk factors [5]. An earlier study similarly concluded that around a third of Alzheimer's disease cases were attributable to modifiable risk factors and estimated that relative reductions of 10% per decade in the prevalence of each of seven key risk factors could reduce Alzheimer's disease prevalence in 2050 by 8.3%[5]. Several healthy living behaviours, such as regular physical exercise, high mental activity and adequate blood pressure control [6], have been recognised as effective risk reduction strategies to delay dementia onset, and are receiving increasing attention in both research and policy [1, 7-10].

Whilst older adults may recognise the link between modifiable risk factors and dementia risk, making and sustaining lifestyle changes is difficult [8]. Innovative initiatives that are less time-intensive, targeting multi-domain lifestyle changes and can be implemented at large-scale to enable individuals to successfully make and sustain changes in their daily routine, is required. One potential approach is to adopt behaviour change principles in public health initiatives. Behaviour change frameworks posit that goal setting and the addition of physical and psychological resources to an individual’s environment can prompt and maintain lifestyle changes [11]. Previously, the most effective interventions to maintain behaviour change in the long-term adopted self-regulation techniques such as goal-setting and progress monitoring strategies [11]. This method was adopted in the Eat Better & Move More (EBMM) program (part of the “Steps to a HealthierUS” public health initiative) which incorporated physical cues (pedometers, tips and task sheets) and information/education resources (guidebooks and mini-talks/videos) to effectively influence behaviour change, with 75% of participants demonstrating improved nutrition and physical activity levels [10]. Thus, creating an educational environment with the provision of mechanisms like physical cues may increase autonomous motivation to adjust habits and patterns [11].

Another important aspect of understanding individual dementia risk is obtaining a cognitive screen. However, there are various barriers to administering and participating in such tests for both clinicians and patients [12-14]. For patients, current health status, societal stigma [15] and pre-existing attitudes, screening pressures, misconceptions and lack of dementia literacy have major implications on seeking a dementia screen [12]. For clinicians, poor prognosis, lack of available treatment options, cost, limited time, and accuracy of the screening tool are significant deterrents to screening operations and follow-ups on positive dementia screens [12]. To address some of these limitations, research into the gamification of cognitive function screeners has seen promising findings. There is evidence to suggest the possibility of memory performance assessed using VR is more reliably associated with general cognitive functioning and may be a more appropriate “age-fair” alternative compared to traditional neuropsychological screens [16]. However, evidence for its acceptance[17], utility and ability to discriminate between age-related cognitive decline and dementia-related cognitive decline across multiple domains is inconsistent and sparse, largely due to studies adopting a cross-sectional design [16, 18].

**Brain Bootcamp**

In response to this backdrop, the *Brain Bootcamp* public health campaign was funded by the New South Wales (NSW) State Government to support healthy and active brain lifestyles and reduce dementia risk in older adults. The delivery of individualised brain health risk score, educational resources and physical items designed to support health-related behaviour change will be packaged in a box and delivered for free to 500 older adults in Sydney, Australia. A sub-set of individuals will also engage in a virtual reality cognitive screener which will help to determine the feasibility of delivering gamified cognitive tests on a larger scale.

In Study 1, our aim is to evaluate the impact of the Brain Bootcamp campaign in reducing dementia risk and improving dementia literacy and knowledge of modifiable lifestyle factors in older Australians. Study 2 aims to understand participants’ views of dementia prevention and explore the acceptability and integration of the intervention into daily life and routine practice. In Study 3, our aim is to determine the feasibility, acceptability and discriminate validity of a virtual reality cognitive screener in a sub-set of older adults.

# 2. HYPOTHESIS

Our hypotheses are that:

1. The Brain Bootcamp campaign will improve older adults’ brain health risk profile at follow-up assessment.
2. The Brain Bootcamp campaign will increase older adults’ dementia awareness and knowledge of modifiable risk factors.
3. The virtual reality cognitive screener is feasible and acceptable for use with younger and older adults.
4. The virtual reality cognitive screener is able to discriminate between cognitively intact and cognitively impaired participants.

# 3. STUDY OBJECTIVES

**Study 1**

### 3.1. STUDY 1 PRIMARY OBJECTIVES

(i) To evaluate the impact of the Brain Bootcamp campaign in increasing dementia awareness and knowledge of modifiable lifestyle factors in older Australians

(ii) To evaluate the impact of the brain bootcamp campaign in improving older adults’ brain health risk profile

**Study 2**

### STUDY 2 PRIMARY OBJECTIVE

To understand participants’ views of dementia prevention and the adoption of Brain Bootcamp into their daily lives.

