**Study 2**

A sample from Study 1’s participants will be invited for semi-structured interviews at the end of the follow-up assessments. Interviews will explore their views of the information they received from their profile, whether they have accessed the resources in their Brain Bootcamp pack, any health behaviour change goals, how they did/did not incorporate recommendations into their daily life, and their perception of the overall impact of the initiative. We will also investigate why participants did not complete the trial by including a sample of those who dropped out.

An opt-in approach to recruitment of participants has been selected, to reduce any perceived pressure, and ensure that clients’ decision to participate is made freely. Participants will receive the following information prior to choosing to take part in the study:

- There will be no consequence or penalty associated with choosing not to participate, including any kind of consequence regarding the Brain Bootcamp box previously sent to them.
- Their responses will remain entirely anonymous, and no individual participant will be identified when reporting results from the interviews and focus groups, or any other data analyses.

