**Study 2**

Participants who wish to participate in a telephone interview will share information on their views of the information they received from their profile, whether they have accessed the resources in their Brain Bootcamp box, any health behaviour change goals, how they did/did not incorporate recommendations into their daily life, and their perception of the overall impact of the campaign. Interviews will be audio recorded and will be sent of a to a professional transcribing service to be transcribed verbatim then the audio-recording destroyed. Typed transcripts will be edited to remove any identifying information. Each interview should take approximately 15 minutes.

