**Study 2**

A semi-structured questioning route beginning with general opening questions and several key questions and sub questions. The questioning route will be organised into themes; (1) Brain Bootcamp overall; (2) Effectiveness of intervention strategies (a) brain health risk profile (b) Brain Bootcamp box items (3) Recommendations and Improvements. Questions have been developed based on feasibility and acceptance interviews employed in previous public health interventions[40-42].

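### The first half of Study 2's only primary objective, views of dementia prevention, is not matched by any listed interview topic, organising theme or outcome

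*Protocol*

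**What the plan says.** Section 3 of the Protocol states one primary objective for Study 2, to understand participants' "views of dementia prevention and the adoption of Brain Bootcamp into their daily lives". The Summary gives the same objective. Section 1, under the Brain Bootcamp subheading, repeats the prevention element: "views of dementia prevention and explore the acceptability and integration of the intervention into daily life and routine practice".

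The interview content is described in several places:

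- **Summary, Study procedure:** the interview is to "explore their views of the Brain Bootcamp Box", and to cover whether behaviour changed and what participants think of the initiative's impact.
- **Section 6.2, Study 2:** "Interviews will explore their views of the information they received from their profile, whether they have accessed the resources in their Brain Bootcamp pack", then "any health behaviour change goals, how they did/did not incorporate recommendations into their daily life", then perceived overall impact. The same paragraph ends: "We will also investigate why participants did not complete the trial by including a sample of those who dropped out".
- **Section 6.6, Study 2:** the same five topics, beginning "views of the information they received from their profile, whether they have accessed the resources in their Brain Bootcamp box, any health behaviour change goals".
- **Section 7, Table 2:** a single Study 2 outcome, covering change in behaviour and the campaign's impact.
- **Section 7, Study 2:** a questioning route organised into three themes: "1) Brain Bootcamp overall; (2) Effectiveness of intervention strategies (a) brain health risk profile (b) Brain Bootcamp box items (3) Recommendations and Improvements".

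Section 6.5 describes the interview to participants, in both the Study 2 overview and the consent text for Studies 1 and 2, as a way of giving feedback on the campaign.

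**The concern.** A qualitative study can report only on what its interviews draw out. If half of the objective has no topic, theme or outcome attached to it, an interviewer who follows the plan has no prompt to raise it, and whether it appears in the transcripts depends on what participants volunteer.

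The two limbs are different subjects. A participant may find the risk profile clear and the box items useful and still believe that dementia cannot be prevented, or the reverse. Product feedback therefore does not stand in for views of prevention. At stake is whether Study 2 can report on the first thing it says it will study. An omission noticed after the interviews could be repaired only by contacting participants again.

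**Working it through.** The plan gives no figure on this point, so nothing is recalculated. The check sets each stated commitment against each description of what is collected.

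**Commitments**

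1. Views of dementia prevention (Summary objectives; section 1; section 3).
2. Adoption of the programme in daily life (same places).
3. Reasons for not completing (section 6.2, last sentence of the first Study 2 paragraph).

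**Coverage**

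| Place in the Protocol | Stated content | Prevention views | Adoption | Reasons for non-completion |
|---|---|---|---|---|
| Summary, Study procedure | box, behaviour change, impact | not named | yes | not named |
| Section 6.2, Study 2 | five topics plus closing sentence | not named | yes | yes, in the closing sentence |
| Section 6.6, Study 2 | the same five topics | not named | yes | not named |
| Section 7, Table 2 | behaviour change and campaign impact | not named | yes | not named |
| Section 7, Study 2 route | three themes | not named | through the profile and box themes | not named |
| Section 6.5, interview purpose | feedback on the campaign | not named | compatible | not named, but drop-outs are to be approached |

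**Count for the prevention limb.** The five topics in sections 6.2 and 6.6 are the profile information, resources accessed, goals, uptake of recommendations and perceived impact: 0 of 5 name prevention views. The three themes in section 7 are the programme overall, effectiveness of the profile and box items, and recommendations: 0 of 3. The Table 2 outcome does not name them either. The nearest topics are opinions on the profile information and the person's own goals. Both are related to prevention, but they concern the material received and the person's conduct, not what the person thinks about preventing dementia.

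**Count for non-completion.** This commitment appears in one description of the interviews (section 6.2) and is supported by recruitment in section 6.5 and by sampling in section 8.1, which includes people who dropped out. It is missing only from the other content lists.

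**Scale.** The mismatch applies to the whole planned set of about 40 interviews of about 15 minutes each, because one questioning route is described for all of them.

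**The case against.** The strongest reply is that the Protocol gives headings, not the interview guide. Section 7 mentions opening, key and sub questions without reproducing them. A heading on the programme overall could hold a prevention question, since the programme exists to reduce dementia risk. Section 8.2 begins with open coding, so subjects that participants raise will be picked up. This stands as far as it goes: it cannot be said that prevention views will be absent. It does not remove the mismatch, because coding works only on what was said, and every stated topic in a short interview points elsewhere.

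A second reply is that Study 1 already gathers related data: survey items on needs, wishes and barriers concerning brain health, and the scale of motivation to change lifestyle for dementia risk reduction (section 7). Section 8.2 also plans to triangulate interview codes with quantitative findings. That is useful context. But those are Study 1 survey instruments, and Study 2 promises a qualitative understanding.

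A reader might also infer more than the text supports:

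- **That reasons for drop-out will go unanswered.** Section 6.2 states them as something Study 2 will investigate, within the paragraph describing the interviews, and sections 6.5 and 8.1 provide for reaching and sampling drop-outs. What remains is a failure to repeat the point in sections 6.6 and 7.
- **That the topics presuppose use of the box and so do not suit drop-outs.** The topics ask whether resources were accessed and how recommendations were or were not taken up. The box follows the baseline survey, and section 6.5 defines drop-outs by the missing three-month update, so by design they will have been sent it.
- **That saturation would be judged on the wrong themes.** Section 8.1 defines saturation by the absence of new themes and does not tie it to the section 7 headings.

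**Conclusion.** The concern holds for one limb of a two-limb objective. Views of dementia prevention are named in the Summary objectives, section 1 and section 3, and in none of the descriptions of interview content, the Table 2 outcome, the organising themes or the stated purpose of the interview. Adoption is covered. Data on the prevention limb are therefore not assured. The documents do not support saying that there will be none.

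The conclusion assumes that the topic lists and themes are a fair guide to what is asked. If the full interview guide already contains a prevention question, what remains is a matter of aligning the Protocol text. No estimate, test or sample size is affected. This is an inexpensive improvement that would let Study 2 answer its own objective, and it is best made before interviewing begins.

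**What to change.** - In section 7, Study 2, add one key-question theme on participants' views of dementia prevention, for example whether they think dementia can be prevented, what would help and what gets in the way. Asking it before the product questions would keep the answers from being framed by the box.
- Add the same topic to the lists in the Summary (Study procedure), section 6.2 and section 6.6.
- Extend the Study 2 outcome in Table 2, and the interview purpose in both parts of section 6.5, so that they are no longer limited to the campaign.
- For consistency, carry the section 6.2 commitment on reasons for non-completion into sections 6.6 and 7.

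A separate interview route for drop-outs or a theme-by-theme saturation rule would be a matter of preference and is not needed to close this gap.

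The cost is a few added questions. Interviews may run slightly over 15 minutes, or some product questions can be trimmed. No extra participants or staff are needed. Section 9.3 requires amendments to be reported to the ethics committee, so the change to the Protocol and consent description would go through that step.

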**Study 3**

### STUDY 3 PRIMARY OBJECTIVES

1. To determine the validity and reliability of new virtual reality cognitive screener in assessing cognitive function in older adults
2. To assess the ability of the virtual reality cognitive screener to discriminate between cognitively intact and cognitively impaired participants.

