**Study 3**

**Inclusion**

- Community-dwelling adults aged 18 and over
- Access to the internet in order to complete virtual reality component
- Living in NSW
- Ability to communicate sufficiently in English

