**Exclusion**

- Unable to provide informed consent
- Diagnosis of dementia
- Diagnosis of severe depression
- Poor vision
- Unable to follow verbal commands
- Diagnosis of aphasia
- Impairment of kinetic abilities (ability to use mouse)

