**Study 3**

General public participants who meet the inclusion criteria and are over the age of 18 will be recruited to participate in both a virtual reality cognitive screener and a traditional telephone based cognitive screening test. For the older adults, a sub-set of older adult participants from Study 1 will be contacted via email to see if they are interested in participating. This will be based on their scores in the brain health risk profile, identified using the LIBRA index, which is shown to be a valid predictor of the development of dementia [19-21]. Younger adults will be recruited from the general public via social media and other relevant channels. All participants will be provided with an opportunity to participate in a feedback survey after they have completed the virtual reality screener. Questions will be about the acceptance, perception and experience of virtual reality.

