**Study 3**

This study requires the general public aged over 65 to undertake a new virtual reality cognitive screener (online) or a telephone-based cognitive assessment. Participants will be required to provide consent for researchers to use the identifiable information provided in study 1 to be contacted to participate in study 2. Therefore, participants are consenting to (1) using identifiable information provided in study 1 to be contacted for study 2; (2) participate in a virtual reality cognitive screener or; (3) participate in a traditional cognitive assessment via telephone (4) participate in an online feedback survey about the acceptability and feasibility of the Virtual Reality Cognitive Screener

Most research involving this population is premised upon the informed consent of the participants. If older participants are not competent enough to make a decision due to cognitive impairments, they will be excluded from the study. This is highlighted in the inclusion criteria.

Participant capacity to consent will be made explicit by them completing the survey and providing the research team with their online consent.

Information sheets and consent forms will provide an explicit outline of the study, participant involvement and expectations with a provision for “opt out” and Project Manager contact details for any queries. These documents will clearly state that the participants may opt out at any time.

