**Study 3**

Descriptive data will be compared between the groups using a two-sample t test and the Fisher exact test for continuous and categorical variables, respectively. Summary statistics will be calculated individually for the Virtual Reality Cognitive Screener, traditional cognitive assessment and questionnaire-dependent feedback scores. Younger and older adults (and older adults with cognitive impairment) cognitive performance on all measures will be compared using the two-sample t tests.

Performance scores will be analysed at each task level, given a total score, and compared between the older cognitive-intact and younger groups using the methods described above, as appropriate. Correlation between performance scores and other variables will assessed using Pearson correlation. A logistic regression will performed based on the total performance scores, followed by ROC analysis to assess its predictive capability to discriminate between cognitively intact and cognitively impaired individuals. Analyses will be performed using SPSS V22.0.

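### Study 3 makes discriminating intact from impaired participants a primary objective, but nothing in its recruitment, sample size or definition of impairment secures enough impaired participants to answer it

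*Protocol*

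**What the plan says.** **Objective.** Section 3 gives Study 3 two primary objectives. The second is "To assess the ability of the virtual reality cognitive screener to discriminate between cognitively intact and cognitively impaired participants". Hypothesis 4 in section 2 states that the screener can do this and sets no AUC threshold.

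**Analysis.** Section 8.2, Study 3: "Younger and older adults (and older adults with cognitive impairment) cognitive performance on all measures will be compared using the two-sample t tests". A logistic regression on the total performance score and an ROC analysis follow, to separate intact from impaired people.

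**Who is recruited.** The Summary and section 4.2 give 100 older and 100 younger adults. The inclusion list in section 5.1 opens with "Community-dwelling adults aged 18 and over" and adds internet access, residence in NSW and English. No impaired group, quota or minimum number is given.

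**Who is excluded.** Section 5.1 lists "Diagnosis of dementia", and also inability to follow verbal commands and inability to use a mouse. Section 6.5 adds: "If older participants are not competent enough to make a decision due to cognitive impairments, they will be excluded from the study".

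**Selection from Study 1.** Section 6.2 says of the invitation to older Study 1 participants: "This will be based on their scores in the brain health risk profile, identified using the LIBRA index". The Summary (Study procedure) widens the basis to baseline assessments together with the dementia risk profile. Neither place gives a direction, cut-off or number.

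**Sample size.** The Study 3 calculation in section 8.1, printed under a second Study 2 heading, is for a biserial correlation of 0.30 with 80% power. It gives 64 per group, raised to 100 for drop-out.

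**Definition of impaired.** Section 7 classifies TICS-M scores above 40 as no or minimal impairment, 20 or below as possible mild impairment, and 12 or below as moderate impairment. It separately uses a score below 27 for referral.

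**The concern.** An ROC analysis gets most of its precision from the smaller of its two classes, here the impaired. The protocol names that class in an objective, a hypothesis and three planned analyses, but does not say where its members come from or how many are expected. The eligibility rules remove the clearest cases, so what remains is milder, undiagnosed impairment among volunteers who are online and can use a mouse.

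If few such people turn up, an AUC that does not clear 0.5 would not show that the screener fails, and a favourable AUC would carry a wide interval. Either way a primary objective would be reported on a number of cases that nobody planned. A later analysis plan cannot repair this, because objectives, eligibility and recruitment are fixed in the protocol.

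**Working it through.** **1. The plan's own figure.** In the point-biserial t-test model, ncp = √(N·ρ²/(1−ρ²)) with N−2 degrees of freedom. With ρ = 0.30 and N = 64, ncp = √(64 × 0.09/0.91) = 2.52. A one-sided 5% test then has power 0.8005, so 64 is reproduced. Two-sided, 82 would be needed (power at 64 is 0.70), and 100 still covers that with up to 18% drop-out. The calculation contains no AUC, sensitivity or number of impaired participants, and the dichotomy in the biserial correlation is not named.

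**2. Precision of the AUC.** The protocol gives no prevalence of impairment. I assume 5, 10, 20 or 30 impaired (n₁) among 100 older adults (n₀ = 100 − n₁) and use the Hanley-McNeil standard error:

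SE² = [A(1−A) + (n₁−1)(Q₁−A²) + (n₀−1)(Q₂−A²)] / (n₁n₀), with Q₁ = A/(2−A) and Q₂ = 2A²/(1+A).

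For A = 0.80, Q₁ = 0.6667, Q₂ = 0.7111 and A² = 0.64. With 5 impaired: [0.16 + 4 × 0.0267 + 94 × 0.0711]/(5 × 95) = 6.951/475 = 0.01463, so SE = 0.121 and the half-width is 1.96 × 0.121 = 0.24. With 10 impaired: 6.729/900 = 0.00748, so SE = 0.086 and the half-width is 0.17.

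**3. Power to exceed 0.5 (two-sided 5%).** Power = Φ[(A − 0.5 − 1.96·SE₀)/SE_A], where SE₀ is the same formula at A = 0.5. For A = 0.70 with 5 impaired: SE₀ = 0.133 and SE_A = 0.134, so (0.20 − 0.261)/0.134 = −0.45 and power = 0.32.

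| Impaired of 100 (assumed) | Half-width, AUC 0.80 | Approx. 95% CI around 0.80 | Power, AUC 0.70 | Power, AUC 0.80 |
|---|---|---|---|---|
| 5 | 0.24 | 0.56–1.00 | 0.32 | 0.63 |
| 10 | 0.17 | 0.63–0.97 | 0.54 | 0.90 |
| 20 | 0.12 | 0.68–0.92 | 0.79 | 0.99 |
| 30 | 0.10 | 0.70–0.90 | 0.90 | about 1.00 |

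The interval with 5 cases is capped at 1. A normal approximation is rough at that count, so that row shows the order of size only. A half-width of 0.10 at AUC 0.80 needs about 33 impaired of 100.

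**4. Would the younger adults help as extra intact controls?** Hardly. With 10 impaired and 190 intact, the half-width at AUC 0.80 is still 0.17.

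**5. Chance variation in the count.** If 5% of older participants were impaired, the central 95% binomial range is 1 to 10 cases; at 10% it is 5 to 16; at 20% it is 12 to 28.

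**6. Who counts as impaired.** The TICS-M bands leave scores from 21 to 40 unclassified. A person scoring 25 is below the referral value but in no impairment band. Counting as impaired those at or below 20, those below 27, or everyone not above 40 could give very different numbers from the same data.

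**The case against.** **Feasibility label.** The Summary and section 4.1 call Study 3 a feasibility study, and a preliminary AUC is an ordinary product of one. This stands, and it is the best argument for an exploratory label. It does not fit with a primary objective and a hypothesis stated without qualification.

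**Enough cases may arise.** A reader might infer that too few impaired participants are bound to appear. The documents do not support that. They give no prevalence, undiagnosed impairment remains eligible, and selection from a Study 1 pool of up to 500 could enrich the sample. With 20 to 30 cases a rough AUC could be estimated. What stands against this is that nothing secures such numbers. Section 6.2 describes LIBRA as predicting later dementia, which is not a measure of present cognition, and the invitation rule has no direction.

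**A high AUC would still mean something.** A reader might also infer that no favourable result could support hypothesis 4. That goes too far: at an AUC of 0.80 the approximate lower limit exceeds 0.5 from 5 cases upwards, and the hypothesis sets no threshold. Nor is the logistic model heavily loaded, since it rests in effect on one predictor.

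**Excluding dementia is defensible.** A screener is meant for undiagnosed people, and adding known cases could inflate the AUC. I accept this; the exclusion itself is not the fault.

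**Background text.** Section 1.1 says that evidence on the ability of VR to "discriminate between age-related cognitive decline and dementia-related cognitive decline across multiple domains is inconsistent and sparse, largely due to studies adopting a cross-sectional design". It is tempting to fault Study 3, itself cross-sectional, for not closing that gap. But this is literature background; the objective and hypothesis speak only of cognitive impairment.

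**Conclusion.** The concern holds in a limited form. Discrimination of intact from impaired participants is a primary objective whose case number is left to chance, whose definition of a case is unsettled, and which the sample size calculation does not visibly address. The number may be too small; the documents do not show that it will be.

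The consequence ranges from serious to modest. With about 5 impaired participants the AUC would be known to roughly ±0.24, with about 30 to roughly ±0.10. If true discrimination is moderate (AUC 0.70), fewer than about 10 cases gives little better than even odds of excluding 0.5. These figures rest on assumed counts, 100 evaluable older adults and the Hanley-McNeil approximation. Drop-out would widen the intervals.

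The protocol should be changed on this point, but the rest of Study 3 is not undermined: the continuous comparison of the two instruments uses every older participant.

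**What to change.** - **Sections 2 and 3:** mark objective 2 and hypothesis 4 of Study 3 as exploratory, in line with the feasibility label.
- **Section 8.2:** make the association of VR score with TICS-M as a continuous score, in all older adults, the primary validity analysis. Both scores are already collected and a Pearson correlation is already planned. By the Fisher z formula a two-sided test of ρ = 0.30 with 80% power needs 85, so 100 older adults allow 15% drop-out.
- **Sections 7 and 8.2:** reconcile the TICS-M bands with the referral value, and state one analysis definition of impaired that covers the whole score range. Which cut-off to use is for the investigators.
- **Section 8.2:** report the AUC with its confidence interval and the number impaired. Make no discrimination claim below a pre-stated minimum number of impaired participants, derived from a precision target. For scale, at AUC 0.80 about 10 cases give ±0.17, 20 give ±0.12 and 33 give ±0.10.
- **Section 6.2:** state how baseline assessments and LIBRA score determine who is invited.

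The cost is protocol wording and a change in the order of analyses, with no extra participants. The downside is that one primary objective becomes exploratory. Keeping it primary would instead require a recruitment source for impaired participants and a number justified by the precision wanted.
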